## Abstract

**Background:**

False messages on the internet continually propagate possible adverse effects of fluoridated oral care products and water, despite their essential role in preventing and controlling dental caries.

**Objective:**

This study aims to evaluate the patterns of psychophysiological reactions of adults after the consumption of internet-based fluoride-related information and disinformation.

**Methods:**

A 2-armed, single-blinded, parallel, and randomized controlled trial will be conducted with 58 parents or caregivers of children who attend the Clinics of Pediatric Dentistry at the Bauru School of Dentistry, considering an attrition of 10% and a significance level of 5%. The participants will be randomized into test and intervention groups, being respectively exposed to fluoride-related information and disinformation presented on a computer with simultaneous monitoring of their psychophysiological reactions, including analysis of their heart rates (HRs) and 7 facial features (mouth outer, mouth corner, eye area, eyebrow activity, face area, face motion, and facial center of mass). Then, participants will respond to questions about the utility and truthfulness of content, their emotional state after the experiment, eHealth literacy, oral health knowledge, and socioeconomic characteristics. The Shapiro-Wilk and Levene tests will be used to determine the normality and homogeneity of the data, which could lead to further statistical analyses for elucidating significant differences between groups, using parametric (Student *t* test) or nonparametric (Mann-Whitney *U* test) analyses. Moreover, multiple logistic regression models will be developed to evaluate the association of distinct variables with the psychophysiological aspects. Only factors with significant Wald statistics in the simple analysis will be included in the multiple models (*P*<.2). Furthermore, receiver operating characteristic curve analysis will be performed to determine the accuracy of the remote HR with respect to the measured HR. For all analyses, *P*<.05 will be considered significant.

**Results:**

From June 2022, parents and caregivers who frequent the Clinics of Pediatric Dentistry at the Bauru School of Dentistry will be invited to participate in the study and will be randomized into 1 of the 2 groups (control or intervention). Data collection is expected to be completed in December 2023. Subsequently, the authors will analyze the data and publish the findings of the clinical trial by June 2024.

**Conclusions:**

This randomized controlled trial aims to elucidate differences between psychophysiological patterns of adults exposed to true or false oral health content. This evidence may support the development of further studies and digital strategies, such as neural network models to automatically detect disinformation available on the internet.

**Trial Registration:**

Brazilian Clinical Trials Registry (RBR-7q4ymr2) U1111-1263-8227; https://tinyurl.com/2kf73t3d

**International Registered Report Identifier (IRRID):**

PRR1-10.2196/39133

## Introduction

Dental caries in children is still a significant public health challenge in distinct populations, affecting 532 million infants worldwide, mainly in socially disadvantaged families [1,2]. Its contemporary management focuses on improving personal dietary and oral hygiene habits, as it is a sugar- and biofilm-driven disease resulting from consecutive dental demineralization processes [2,3]. In this context, fluoride-containing oral care products and drinking water play an important role in preventing dental demineralization and promoting remineralization [4-6]. Nevertheless, false or misleading content on the internet continually propagates the discouragement of fluoride usage because of possible adverse health effects [7], which supports the development of dental beliefs that could negatively impact parental oral health behaviors [8]. At the same time, fluoride refusal is a growing concern observed in pediatric dental offices, probably driven or reinforced by internet-based disinformation [9].

Indeed, diverse aspects such as innovative messages, information overload, and predisposed personal characteristics such as pre-existing beliefs, ideological motivations, and political polarization influence the spread of false or misleading web-based content [10-13]. Concurrently, digital users tend to interact with posts associated with their interests uncritically, reinforcing the emergence of echo chambers on social media [13-15]. On the other hand, people may also be susceptible to persuasive information slightly misaligned with their current motivations and behaviors (eg, falsehoods formulated to deceive called disinformation) [16,17]. This process of cognitive dissonance can cause different emotional reactions starting from discomfort or stress to a counterreaction depending on the threat to the individual’s freedom, a response known as psychologic reactance [16,18,19]. Interestingly, people with motivations more aligned to the values of persuasion messages exhibit less physiological arousal than less-aligned individuals [16]. Additionally, American adults likely to believe in conspiracy theories have more stressful life events and more significant perceived stress [20]. Nevertheless, the users' emotional reactions during the consumption of internet-based oral health information and disinformation remain uncertain.

Therefore, this study aims to evaluate the patterns of psychophysiological reactions of adults after the consumption of internet-based fluoride-related information and disinformation. The hypothesis (*H_1_*) for this randomized controlled trial indicates that there are differences in the psychophysiological reactions of adults exposed to oral health information and disinformation.

## Methods

### Trial Design

A 2-armed, single-blinded, parallel, and randomized controlled trial (trial registration number: U1111-1263-8227) will be conducted with 58 parents or caregivers of children who attend the Clinics of Pediatric Dentistry of the Bauru School of Dentistry, considering an attrition of 10% and a significance level of 5%. The participants will be randomized into test and intervention groups, being respectively exposed to fluoride-related information or disinformation presented on a computer, with simultaneous monitoring of their psychophysiological reactions, such as heart rate (HR) and 7 facial features (mouth outer, mouth corner, eye area, eyebrow activity, face area, face motion, and facial center of mass). Then, the participants will respond to questions about the utility and truthfulness of content, their emotional state after the experiment, eHealth literacy, oral health knowledge, and socioeconomic characteristics. The Shapiro-Wilk and Levene tests will be used to determine the normality and homogeneity of data, which could lead to further statistical analyses for elucidating significant differences between groups using parametric (Student *t* test) or nonparametric (Mann-Whitney *U* test) analyses. Moreover, multiple logistic regression models will be developed to evaluate the association of distinct variables with the psychophysiological aspects. Only factors with significant Wald statistics in the simple analysis will be included in the multiple models (*P*<.2). Furthermore, receiver operating characteristic (ROC) curve analysis will be performed to determine the accuracy of F_9_ (remote HR) concerning F_8_ (measured HR). For all analyses, *P*<.05 is considered significant.

This protocol is written according to the SPIRIT (Standard Protocol Items for Clinical Trials) guidelines. Figure 1 depicts the study design synthesis [21]. The peer review reports are available in Multimedia Appendices 1 and 2.

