#### Intervention

The experiments will be conducted based on the methodology described by Kirkwood and Minas [22]. After agreeing with the terms and signing the free consent form, the participants will be led to a silent room and will sit in front of a computer. At this moment, the researcher will instruct the participants about the test functioning (consumption of fluoride-related digital content), highlighting the presentation format and time and explaining the technical issues regarding the capture of psychophysiological reactions, besides encouraging them to persist until the end of the activity, and maintain the sitting posture during the process. To monitor the HR (1 Hz), the participants will be asked to wear 2 digital sports watches (Polar Ignite 2 and Polar Verity Sense) positioned at 7 cm away from their wrists. The HRs captured by Polar Ignite 2 will be used in the analyses, whereas the HRs captured by Polar Verity will be recorded as backup measurements.

Throughout the experiments, a camera (Canon Vixia HF R800 Full HD) will record the participants’ facial expressions. The camera will be placed on a tripod to remain slightly slanted upward and placed to face people at approximately 0.6 m. The video will be recorded in color at 60 frames per second (fps) with a resolution of 1920 × 1080 pixels and saved in the AVCHD-HD format. In addition, a spotlight will be positioned 1.6 m from participants and 45 cm above the camera level to avoid shadows on their faces during the recording. To standardize the recording of the videos, a white photographic background will be positioned approximately 60 cm behind the participants.

Initially, the psychophysiological reaction of participants will be monitored for 150 seconds while they watch a relaxing video with a classical music piece playing in the background (baseline). Next, the monitor will show 25 messages containing fluoride-related information (control) or disinformation (test) in a 6.25-minute slide presentation (15 seconds to read each message).

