**Truthfulness**		
	5. Have you already read or heard about these messages before this research?	Yes
		No
	6. How do you classify most of these messages?	True
		False

Brazilian version of the eHealth Literacy Scale questionnaire presented in English.I know how to find helpful health resources on the Internet.I know how to use the Internet to answer my questions about health.I know what health resources are available on the Internet.I know where to find helpful health resources on the Internet.I know how to use the health information I find on the Internet to help me.I have the skills I need to evaluate the health resources I find on the Internet.I can tell high-quality health resources from low-quality health resources on the Internet.I feel confident in using information from the Internet to make health decisions.

Questionnaire about oral health knowledge of parents or caregivers.The child who is breastfeeding does not need to eat any other type of food until the six months old.Up to six months old, even breastfeeding, the baby also needs to ingest water.After six months old, the baby should eat foods other than maternal milk.After six months old, the baby should no longer drink breast milk.After one year, the baby can taste foods containing sugar.The best way to give teas and juices to babies is using a bottle.After six months old, the baby can be bottle-fed overnight or as much as you want.While the child has baby teeth, it should wear a piece of diaper moistened with filtered water for clean teeth.Babies under two years of age can use the same toothpaste as the adults.Note: Questionnaire proposed by Vilella et al [29] 

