#### Outcomes

The primary outcomes will be obtained by comparing the psychophysiological reactions and self-reported emotional states of participants, as well as the self-perception of the utility and truthfulness of the content between the 2 groups.

The secondary outcomes will be related to sociodemographic characteristics, eHEALS scores, and oral health knowledge of the participants, and these are considered possible confounding factors of primary outcomes.

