### Participant Recruitment Timeline

The participants will be recruited from June 2022 to December 2023. As all data will be collected simultaneously, the enrollment process will require only 1 visit from each participant.

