## Discussion

### Principal Findings

To the best of our knowledge, it is the first study that will evaluate the differences in psychophysiological reactions of internet users exposed to or not exposed to disinformation. Given the proposed hypothesis, we expect that individuals exposed to fluoride-related disinformation will present more psychophysiological reactions during the experiments because of stressors provided by the consumption of novel content. Additionally, those who disagree with the content due to previous health beliefs tend to show more psychophysiological reactions, also considering the cognitive dissonance process [16]. Moreover, it is expected that younger adults with higher levels of eHealth literacy and oral health knowledge probably will feel less persuaded by disinformation than their older counterparts. Finally, we hope to obtain promising results pertaining to the comparison of F_9_ (remote HR) to F_8_ (measured HR), enabling remote validation and measurement of this parameter in future studies on information disorder.

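### eHEALS and oral health knowledge are measured only after the randomised messages but labelled as confounders; an arm effect adjusted for them can be biased, while the planned unadjusted tests are not affected

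*Protocol article*

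**What the plan says.** The Trial Design section describes exposure with simultaneous monitoring, and next has participants answer questions on whether the content is useful and true, and on "their emotional state after the experiment, eHealth literacy, oral health knowledge, and socioeconomic characteristics". The recruitment timeline allows no other occasion: "As all data will be collected simultaneously, the enrollment process will require only 1 visit from each participant". The only measurement described before the messages is physiological (Intervention section): "Initially, the psychophysiological reaction of participants will be monitored for 150 seconds while they watch a relaxing video".

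The Outcomes section gives the same scores two roles. First: "The secondary outcomes will be related to sociodemographic characteristics, eHEALS scores, and oral health knowledge of the participants". Then, in the same sentence: "these are considered possible confounding factors of primary outcomes". The Questionnaires section presents literacy and knowledge as characteristics that influence how people take in and criticise digital content, that is, as prior traits.

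The analysis paragraph under Data Collection, Management, and Analysis compares the arms by Student t or Mann-Whitney U test. Separately, it plans multiple logistic models relating distinct variables to the psychophysiological aspects, with entry at a univariable Wald P<.2. It does not say whether arm is a term in those models.

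**The concern.** A confounder of a randomised exposure would have to precede it. Here both scores follow it, so they may partly be results of the arm. The eHEALS is self-rated, and its closing items ask about evaluating resources, telling good from poor ones, and trusting one's own use of them, for example "I feel confident in using information from the Internet to make health decisions". Participants answer these minutes after reading 25 true or 25 false messages. The Hazards section itself accepts that participants may be left confused about what to trust. That section places the debriefing after the intervention without saying whether it comes before or after the questionnaires. The Implementation section has the questionnaires administered by the examiner who knows the allocation.

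At stake are the regression results. If arm is in a model with a shifted score, the adjusted arm effect can be biased. If arm is left out, it becomes a possible common cause of score and outcome, and the score-outcome association can be distorted. The timing cannot be repaired later: no analysis plan can turn a post-exposure score into a baseline value.

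**Working it through.** The plan gives no figure for an adjusted arm effect, so there is none to reproduce. The check asks how far such an effect would move.

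**Inputs from the protocol.** N = 58, 10% attrition, equal allocation. Completers: 58 × 0.9 = 52.2, taken as 52, or 26 per arm. (Whether 58 follows from the stated effect size is a separate matter.) For scale, at two-sided 5% and an assumed 80% power, 26 per arm detect (1.96 + 0.84) × √(2/26) = 0.78 SD.

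**Assumed inputs, not in the documents.** The messages shift the measured score by s SD (0.25 to 0.5). The underlying score correlates ρ with the outcome (0.3 to 0.5). The true arm effect is zero.

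**Arm in the model.** Let A be arm, L the score before exposure, and M = L + sA the score as measured. If the outcome is Y = ρL + error, substituting L = M − sA gives Y = ρM − ρsA + error. Adjusting for M therefore produces an arm coefficient of −ρs where the truth is zero. The sign depends on the signs of s and ρ.

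This was checked by simulation: 52 completers, a continuous outcome and 4,000 replicates per row. The odds ratios come from a large-sample logistic fit with the outcome split at its median and a true value of 1.0.

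| s | ρ | ρ × s | Simulated adjusted arm effect (SD) | Type I error, adjusted | Type I error, unadjusted t test | Adjusted OR |
|---|---|---|---|---|---|---|
| 0 | 0.3 | 0 | 0.00 | 5.2% | 5.6% | 1.0 |
| 0.25 | 0.3 | 0.075 | −0.08 | 5.6% | 4.7% | 0.89 |
| 0.25 | 0.5 | 0.125 | −0.12 | 8.0% | 5.1% | 0.78 |
| 0.5 | 0.3 | 0.15 | −0.15 | 7.8% | 4.9% | 0.77 |
| 0.5 | 0.5 | 0.25 | −0.26 | 18.2% | 4.6% | 0.62 |

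Simulation error on a 5% rate is about √(0.05 × 0.95/4000) = 0.3 percentage points, so the 5.6% in the mildest shifted row is barely distinguishable from 5%. The unadjusted test holds its level throughout. With ρ = 0 the adjusted effect is also unbiased, whatever the shift.

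**Arm left out of the model.** Suppose the true arm effect is τ and the score is unrelated to the outcome (ρ = 0). With equal allocation, Var(A) = 0.25, and the slope of Y on M is 0.25 × s × τ / (1 + 0.25 × s²). At s = 0.5 and τ = 0.78 this is 0.0975 / 1.0625 = 0.09. That is an apparent association of 0.09 outcome SD per unit of score (scaled in SDs of L) where none exists.

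**Entry rule.** Selection at P<.2 does not look at timing. It favours scores that are associated with the outcome, which is the condition under which the first bias can occur.

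**The case against.** The strongest reply is that the protocol assigns the comparison of arms to unadjusted tests, and questionnaire order cannot bias those. This stands, and the table shows it. A reader might infer that the trial's main arm effect is biased; the documents do not support that. Nor does the protocol say that the logistic models contain arm, that they supply the arm effect, or that these two scores must enter. The point is therefore about an adjusted effect if one is estimated, and about the score associations if arm is omitted.

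The mechanism is also weaker for knowledge. One of its nine items concerns toothpaste; the rest cover breastfeeding, water, other foods, sugar, bottles and cleaning with a cloth. Fluoride messages have little obvious route to that total. This stands too, and leaves the eHEALS as the main exposure. Even there the items concern general internet skills, and a shift of half an SD after a session of about six minutes is an assumption.

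A reader might go further and take the Discussion's expectation that "younger adults with higher levels of eHealth literacy and oral health knowledge probably will feel less persuaded by disinformation" as proof that the planned models lack needed arm-by-covariate interactions. That does not follow. The protocol names no interaction but excludes none, and model terms are commonly left to an analysis plan that is not shown here. The stated hypothesis is an arm difference only. The expectation concerns persuasion, not the psychophysiological outcomes of the described models, and could be examined within the disinformation arm.

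Finally, asking about information quality just before the messages may prime scrutiny, possibly more for false messages than for true ones. That is a real trade-off. It does not bear on the alternative of leaving the order alone and not adjusting.

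**Conclusion.** The point holds in limited form. Both scores are post-exposure measurements, have no pre-exposure counterpart, and are called confounders and secondary outcomes at once. Used as labelled, they can bias an adjusted arm effect by about ρ × s: roughly 0.08 to 0.26 outcome SD for s from 0.25 to 0.5 and ρ from 0.3 to 0.5, against a detectable difference of about 0.78 SD. The bias is zero if the messages do not move the score or the score is unrelated to the outcome.

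The size rests wholly on assumed values and on a linear model in which only the pre-existing score drives the outcome. If the shift itself affects the outcome, adjustment instead removes part of the arm's effect. The logistic check points the same way. The planned unadjusted comparison is sound on this point, and no conclusion about missing interaction terms is drawn.

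**What to change.** Administer the eHEALS, the knowledge questionnaire and the sociodemographic questions after consent and before the 150-second baseline video. Keep only the six Table 1 items after exposure. In the Outcomes section, relabel the scores as baseline covariates and remove them from the secondary outcomes.

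For participants already enrolled in the current order, or for everyone if priming is judged the greater worry, keep the arm comparison unadjusted for these two scores. Report their associations with the outcomes from models that include arm, described as post-exposure measures.

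The cost is a change in the order of forms within the same visit. The downside is possible slight priming on health information, which might not be exactly equal across arms; the relaxing video between forms and messages gives some buffer. The no-adjustment route has no priming cost, but it leaves the trial without a baseline measure of either trait.

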**Figure 1 figure1:**
[figure not shown]
Study flowchart.

### Participants, Intervention, and Outcomes

#### Study Setting

The study will be conducted in a reserved and silent room in the Department of Pediatric Dentistry at the Bauru School of Dentistry in the University of São Paulo, Brazil. The parents and caregivers of children who attend the Clinics of Pediatric Dentistry will be invited to participate in the study.

#### Eligibility Criteria

The participants will be recruited according to the following inclusion criteria: (1) should be parents or caregivers of children who attend the Clinics of Pediatric Dentistry of the Bauru School of Dentistry, (2) should be native Brazilians, (3) should be literates, (4) should have regular access to the internet, and (5) should agree with terms and sign the free consent form. On the other hand, people who decide to withdraw the previously signed free consent form will be excluded from the study.

#### Intervention

The experiments will be conducted based on the methodology described by Kirkwood and Minas [22]. After agreeing with the terms and signing the free consent form, the participants will be led to a silent room and will sit in front of a computer. At this moment, the researcher will instruct the participants about the test functioning (consumption of fluoride-related digital content), highlighting the presentation format and time and explaining the technical issues regarding the capture of psychophysiological reactions, besides encouraging them to persist until the end of the activity, and maintain the sitting posture during the process. To monitor the HR (1 Hz), the participants will be asked to wear 2 digital sports watches (Polar Ignite 2 and Polar Verity Sense) positioned at 7 cm away from their wrists. The HRs captured by Polar Ignite 2 will be used in the analyses, whereas the HRs captured by Polar Verity will be recorded as backup measurements.

Throughout the experiments, a camera (Canon Vixia HF R800 Full HD) will record the participants’ facial expressions. The camera will be placed on a tripod to remain slightly slanted upward and placed to face people at approximately 0.6 m. The video will be recorded in color at 60 frames per second (fps) with a resolution of 1920 × 1080 pixels and saved in the AVCHD-HD format. In addition, a spotlight will be positioned 1.6 m from participants and 45 cm above the camera level to avoid shadows on their faces during the recording. To standardize the recording of the videos, a white photographic background will be positioned approximately 60 cm behind the participants.

Initially, the psychophysiological reaction of participants will be monitored for 150 seconds while they watch a relaxing video with a classical music piece playing in the background (baseline). Next, the monitor will show 25 messages containing fluoride-related information (control) or disinformation (test) in a 6.25-minute slide presentation (15 seconds to read each message).

Each slide will show a short and straightforward message (maximum of 200 characters) for 15 seconds, which is sufficient for the participants to read and understand it [23]. The slides will be developed with a white background and contain messages in black font. By default, the messages will be aligned at the center of the slides. Additionally, the messages will be related to the main issues that emerged from a previous characterization of false or misleading fluoride-related posts on social media [24]. In this regard, we will format the original content of false or misleading posts (intervention group) to ensure a better simulation of the digital environment. Despite the difficulties in classifying distinct information disorder types, the intervention group participants will only receive disinformation because they are intended to deceive individuals intentionally [17].

At the end of the experimental session, the same video used to collect baseline data will be made available to participants for an additional 150 seconds to measure the variations in the psychophysiological parameters.

